### Sample size calculation

2.3

An *a priori* power analysis was performed using JASP (version 0.19.2) to estimate the required sample size for detecting a between-group difference in biomarker levels with adequate statistical power. Assuming a one-sided independent samples *t*-test, a medium effect size (Cohen's |*δ*| = 0.5), a Type I error rate (*α*) of 0.05 and a target power (1−*β*) of 0.95, the analysis indicated that a minimum of 66 participants in the ICP-exposed group and 132 in the unexposed group would be required to achieve an actual power of 0.952.

These parameters were selected to align with the study's directional hypothesis that intrahepatic cholestasis of pregnancy is associated with poorer respiratory outcomes and higher biomarker levels. A 2:1 unexposed-to-exposed ratio was adopted to address the lower expected incidence of neonates with maternal ICP, providing greater statistical precision while also enhancing generalizability and minimizing bias, without placing disproportionate demands on recruitment. Also, the higher power threshold of 0.95 was chosen to ensure adequate sensitivity for detecting clinically meaningful biomarker differences, which represent a novel co-primary objective and a central component of the study's design.

This configuration provides robust power to detect moderate effect sizes over 0.5 with high reliability, acknowledging that smaller effects (|*δ*| ≤ 0.25) are associated with a substantially reduced probability of detection. Accordingly, a minimum of 198 neonates will be enrolled to meet the sample size requirements established by the power analysis.

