### Statistical analysis

2.8

Statistical analysis will be performed using JASP 0.19.2. Frequency analysis will be performed using contingency tables. Group differences in the incidence of RDS and the need for surfactant therapy will be assessed using the chi-squared test or Fisher's exact test, where expected cell counts are less than five. Differences in mortality will be evaluated descriptively using odds ratios (ORs), and if event frequency permits, time-to-event analysis may be considered. In addition, time-to-event outcomes such as time to first surfactant dose, time to intubation and time to second surfactant administration will be analyzed using Kaplan–Meier curves and compared using the log-rank test, with Cox regression models applied where appropriate.

Serum biomarker levels indicative of lung injury will be compared between groups at each time point using the Student's *t*-test for normally distributed data or the Mann–Whitney *U* test when normality is not assumed. To assess longitudinal trends in biomarker levels, repeated-measures ANOVA or linear mixed-effects models will be employed, depending on data distribution and completeness. For non-parametric repeated data, the Friedman test may be used. Normality and homogeneity of variances will be tested using the Shapiro–Wilk and Brown-Forsythe tests, respectively. A significance level of 0.05 will be used for all analyses. For normally distributed biomarker data, standardized mean differences between groups will be reported as Cohen's d and Glass's delta. To account for potential residual confounding, gestational age at birth, matched during enrollment, will additionally be included as a covariate in relevant statistical models and stratified analyses may be performed to explore outcome differences across gestational age subgroups.

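### The biomarker t-test is chosen on normality alone: with 66 exposed and 132 unexposed infants, Student's t misses its 0.05 level if the SDs differ, and Welch's test removes that risk at almost no cost

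*Protocol article*

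**What the plan says.** Section 2.8 (Statistical analysis) of the protocol article states that "Serum biomarker levels indicative of lung injury will be compared between groups at each time point", using "Student's *t*-test for normally distributed data or the Mann–Whitney *U* test when normality is not assumed". Normality is the only switch. Later in the section comes the sentence "Normality and homogeneity of variances will be tested using the Shapiro–Wilk and Brown-Forsythe tests, respectively". Nothing says what changes if the variances are found to differ, and Welch's test is not mentioned. The section also sets the level: "A significance level of 0.05 will be used for all analyses". It does not say whether the tests are one- or two-sided.

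Section 2.3 (Sample size calculation) bases the study on this comparison. It reads "Assuming a one-sided independent samples *t*-test", with a standardised difference of 0.5 and target power 0.95, and concludes that "a minimum of 66 participants in the ICP-exposed group and 132 in the unexposed group would be required". The imbalance is deliberate: "A 2:1 unexposed-to-exposed ratio was adopted". The same section describes the biomarker differences as a co-primary objective.

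**The concern.** Student's t-test pools the two variances, and the larger group dominates the pool. With equal group sizes this does little harm. With a 2:1 split, a larger SD in the smaller group makes the pooled standard error too small, so the test rejects too often. A smaller SD in that group makes the test reject too rarely. Here the smaller group is the exposed one.

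The plan looks for unequal variances and then, as written, does nothing about them. The comparison affected is a co-primary objective and the basis of the sample size. An understated standard error would overstate the evidence for lung injury. It would also shorten any pooled-variance confidence interval, whatever the true difference in means.

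**Working it through.** **Inputs from the documents.** n₁ = 66 exposed, n₂ = 132 unexposed, d = 0.5, one-sided α = 0.05, stated power 0.952 (section 2.3); level 0.05, sidedness not stated (section 2.8).

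**Assumed input.** The documents give no SDs. Let r be the exposed SD divided by the unexposed SD. It is varied from 0.5 to 3, with normal data (the case in which the plan uses Student's t) and equal means (the null hypothesis).

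**Step 1: reproduce the plan's power.** The noncentrality is 0.5 × √(66 × 132 / 198) = 0.5 × √44 = 3.317. With 196 degrees of freedom and one-sided α = 0.05, the exact noncentral t gives power 0.9516. With 65 and 130 infants it gives 0.9490. So 66 and 132 is the minimum, and the stated 0.952 is right. This calculation assumes a common SD.

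**Step 2: level of Student's t when the SDs differ.** With the unexposed SD set to 1:

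- True variance of the mean difference: V = r²/66 + 1/132.
- Variance that the pooled test expects: P = [(65r² + 131)/196] × (1/66 + 1/132).
- Large-sample error: 1 − Φ(1.645 × √(P/V)) one-sided, and 2 × [1 − Φ(1.960 × √(P/V))] two-sided.

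For r = 1.5, V = 2.25/66 + 1/132 = 0.04167 and P = (277.25/196) × 0.02273 = 0.03215. Then √(P/V) = 0.878, so the standard error is about 12% too small. The two-sided error is 2 × [1 − Φ(1.722)] = 8.5%, and the one-sided error is 1 − Φ(1.445) = 7.4%.

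The formula and a simulation of 100,000 trials per setting agree:

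| r | √(P/V) | Student two-sided, formula / simulated | Student one-sided, formula / simulated | Welch two-sided, simulated |
|---|---|---|---|---|
| 0.5 | 1.226 | 1.6% / 1.7% | 2.2% / 2.2% | 4.9% |
| 1.0 | 1.000 | 5.0% / 4.9% | 5.0% / 4.9% | 4.9% |
| 1.25 | 0.929 | 6.9% / 6.9% | 6.3% / 6.4% | 4.9% |
| 1.5 | 0.878 | 8.5% / 8.5% | 7.4% / 7.5% | 5.0% |
| 2.0 | 0.815 | 11.0% / 11.2% | 9.0% / 9.2% | 5.2% |

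A separate simulation gave 6.7%, 8.4% and 11.0% two-sided at r = 1.25, 1.5 and 2. At r = 3 the simulated error is 13.7% two-sided and 10.5% one-sided.

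**Step 3: is the imbalance the cause?** With 99 infants per group, the simulated two-sided error of Student's t is 4.8% at r = 1.5 and 5.1% at r = 2. The excess comes from the 2:1 split.

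**Step 4: what if Brown-Forsythe triggered Welch?** The variance test is positive in 48%, 93% and nearly 100% of trials at r = 1.25, 1.5 and 2. The two-sided error of the two-step rule is then 5.7%, 5.2% and 5.2%.

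**Step 5: cost of Welch by default.** With equal SDs and d = 0.5, simulated one-sided power is 0.952 for both tests. With unequal SDs Welch rejects less often. At r = 1.5 and a difference of 0.5 root-mean-square SDs, one-sided power is 0.928 for Welch and 0.954 for Student. Student's advantage there comes with a one-sided error of 7.5% in place of 5%, so it is not a real gain.

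**The case against.** **The exposed group may not be more variable.** This is the strongest objection, and it stands. A reader might infer inflation from the study's hypothesis: higher biomarker levels are expected in exposed infants, spread often rises with level, and so the smaller group would be the more variable. That does not establish a false-positive problem. Type I error is defined at equal means, and if spread follows level, equal means imply equal spread. Inflation needs exposed infants to be more variable at the same mean. A mix of mild and severe bile acid exposure could produce that, but the documents neither show it nor give any SD. Matching on gestational age, birthweight and sex (section 2.4) would tend to even out spread from those sources.

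**Skewed data would not reach Student's t.** This is largely right. In a simulation of lognormal data at these group sizes, both groups passed Shapiro–Wilk about 2% of the time at a coefficient of variation of 0.3, and never at 0.5 or 0.8. The plan would then use Mann–Whitney, so the table applies only to roughly normal biomarkers. Mann–Whitney is not immune either: with normal data its two-sided error is about 7% at r = 1.5 and 9% at r = 2.

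**The variance test may be meant to select Welch, with the detail left to a fuller document.** This is possible, and reporting Glass's delta beside Cohen's d (section 2.8) suggests that unequal SDs were considered. Step 4 shows that such a rule would leave little inflation, so preliminary variance testing cannot be called seriously unreliable here. But the article does state its test and its switch, and the switch is normality alone. Followed as written, the plan leads to Student's t. An analyst who changes to Welch makes an unwritten choice after seeing the data.

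**Conclusion.** The point holds as a conditional weakness. The stated rule uses a pooled-variance test in a deliberately unbalanced design and gives its variance check no consequence. For normal data with equal means, the error is about 6.7–6.9%, 8.5% and 11% two-sided at assumed SD ratios of 1.25, 1.5 and 2, or about 6.3%, 7.5% and 9% one-sided. If the ratio is below 1 the test is conservative: about 1.7% two-sided and 2.2% one-sided at 0.5.

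A reader might infer that the co-primary biomarker result will carry an inflated false-positive rate. The documents do not support that, because they give no SDs and the direction of any difference is unknown. The figures also assume the enrolled 66 and 132. Later samples depend on clinical indication (section 2.5), so the imbalance at 48–72 h and day 7 may differ. The case for change is that Welch holds its level at 4.9–5.2% two-sided over the whole range tried and loses essentially no power when the SDs are equal.

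**What to change.** In section 2.8, name Welch's t-test in place of Student's t-test as the default for normally distributed biomarker comparisons at each time point, and say that the choice does not depend on the variance test. Brown-Forsythe may stay as a check for the repeated-measures ANOVA or as description. Whether the tests are one- or two-sided should be stated in the same place.

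This does not alter the Mann–Whitney branch, which keeps its own sensitivity to unequal spread. Log transformation, if fixed in advance, and heteroscedasticity-robust standard errors in models with gestational age are optional extras.

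The cost is one sentence and no change in sample size. The Discussion plans a preliminary biomarker analysis once 60 participants are enrolled and already reports 54 exposed neonates recruited, so the change is best made before any biomarker data are compared by group.

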### Study objectives

2.2

The primary objectives of this study are to evaluate the incidence of RDS, to assess the need for exogenous surfactant administration and to compare serum biomarker profiles indicative of surfactant dysfunction and pulmonary injury between ICP-exposed and unexposed neonates.

For clarity, these are defined as follows:

RDS is defined as a clinical diagnosis made within the first 72 h of life, based on signs of respiratory compromise (tachypnea, grunting, nasal flaring, chest retractions), supportive radiographic findings and a need for supplemental oxygen or respiratory support.

Surfactant administration refers to any administration of exogenous surfactant therapy within the first 72 h of life, regardless of dosing or mode of delivery.

Biomarker profile includes the quantitative assessment of serum biomarkers related to pulmonary injury and surfactant deficiency, measured at 24 h, 48–72 h and on day 7 of life when available.

Secondary objectives include evaluating respiratory morbidity, such as the need for mechanical ventilation and non-invasive respiratory support, as well as the occurrence of serious respiratory complications including pneumothorax, pulmonary hemorrhage and persistent pulmonary hypertension. Additional secondary objectives include assessing neonatal intensive care unit (NICU) admission, length of hospitalization and in-hospital neonatal mortality.

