### Sample processing

2.6

Following blood collection, samples will be immediately transported to the central laboratory for processing. Centrifugation will be performed using an Orto Alresa Microcen 23 centrifuge, operated at 4,000 revolutions per minute (rpm) for 10 min, under room temperature conditions. After centrifugation, the separated serum will be transferred into a single, pre-labeled Eppendorf tube for each participant. All samples will be stored at −50 °C until further analysis. No aliquoting will be performed and all samples will remain under uniform storage conditions throughout the study duration to minimize pre-analytical variability. Upon completion of recruitment, stored serum samples will undergo batch analysis to quantify selected biomarkers associated with surfactant deficiency and pulmonary injury. Quantitative evaluation will be conducted using commercially available sandwich enzyme-linked immunosorbent assay (ELISA) kits validated for use in human serum. To safeguard the novelty of this research, the specific biomarkers evaluated will be disclosed following validation and publication of study findings.

To ensure participant anonymity and maintain blinding during laboratory analyses, each sample will be labeled using a unique alphanumeric code. The coding format will be as follows: “CS” for neonates born to mothers with cholestasis or “FC” for those born to mothers without liver disease, followed by the first initial of the neonate's last name, an optional number for multiple births (1, 2, or 3 for twin or triplet order), a gender identifier (5 for male, 6 for female), and the date of birth in the format DDMM. For example, a male neonate, twin 1, born to a mother with cholestasis, with the last name Niculae, and born on 21st of May, would be assigned the code CSN152105. This code will be recorded on both the primary collection tube and the Eppendorf storage tube. The code list will be securely maintained by the principal investigator, and laboratory personnel responsible for biomarker analysis will remain blinded to the clinical identity and group assignment of each participant.

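### Three primary objectives, one of them an undisclosed set of biomarkers at up to three time points, are all tested at 0.05 with no lead test, success rule or multiplicity control, so the family-wise error rate is uncontrolled

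*Protocol article*

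**What the plan says.** Section 2.2 (Study objectives) gives three primary aims: "The primary objectives of this study are to evaluate the incidence of RDS, to assess the need for exogenous surfactant administration and to compare" (the comparison is of marker profiles in the two groups). It defines the profile as several serum markers, "measured at 24 h, 48–72 h and on day 7 of life when available". Section 2.3 (Sample size calculation) sizes the study on biomarker differences, "which represent a novel co-primary objective and a central component of the study's design", using a single one-sided t-test at 0.05.

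Section 2.6 (Sample processing) does not name the markers: "the specific biomarkers evaluated will be disclosed following validation and publication of study findings". Section 2.8 (Statistical analysis) tests RDS and surfactant use separately by chi-squared or Fisher's exact test. For the markers it says: "Serum biomarker levels indicative of lung injury will be compared between groups at each time point". It then sets the threshold: "A significance level of 0.05 will be used for all analyses".

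The article names no lead biomarker, no lead time point, no order of testing and no rule for when the primary aim is met. The Discussion adds a preliminary biomarker analysis once 60 participants are enrolled, with interim results to be presented at a conference.

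**The concern.** Each primary test has its own 5% chance of a false positive, and the number of such tests is unknown to any reader. The biomarker objective is where this matters most. It set the sample size, it is the novel part of the study, and it contributes most of the tests. If one analyte at one time point reaches significance, a reader of the final paper cannot tell from the public protocol whether that comparison was the planned main one or one of many.

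This is more than detail that an article leaves to an analysis plan. The article itself assigns 0.05 to every analysis, so a later plan that adjusted for multiplicity would contradict it. It also states, as a deliberate choice, that the list stays undisclosed until publication. The planned early look at 60 participants makes the timing pressing, because results could be seen and presented before any list is on public record.

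**Working it through.** **Inputs from the protocol.** Three primary objectives (2.2); two clinical tests, RDS and surfactant use (2.8); biomarkers tested at up to three time points (2.2, 2.8); 0.05 for every test (2.8); 66 exposed and 132 unexposed, δ = 0.5, one-sided α = 0.05, stated power 0.952 (2.3).

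**Assumptions.** The number of biomarkers, k, is not given. The plural wording implies at least 2, and I use 2 to 5. I also assume that all null hypotheses are true and that any one significant primary test counts as success.

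**Step 1: the plan's own figure.** The noncentrality is δ·√(n₁n₂/(n₁+n₂)) = 0.5·√(66·132/198) = 0.5·√44 = 3.317, with 196 degrees of freedom. Noncentral-t power at one-sided 0.05 is 0.9516, which agrees with the stated 0.952. It covers one comparison at the full 0.05. Section 2.8 does not state sidedness; the two-sided power for the same numbers is 0.910.

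**Step 2: error rate under independence.** With m tests the chance of at least one false positive is 1 − 0.95^m. One biomarker at one time gives m = 3 and 1 − 0.95³ = 14.3%. With all three times, m = 2 + 3k.

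**Step 3: error rate with correlation.** RDS and surfactant use overlap, and repeated samples come from the same neonate, so independence is an upper case. I used simulated equicorrelated normal test statistics (200,000 draws, two-sided 0.05).

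| k | m = 2 + 3k | independent | correlation 0.5 | correlation 0.8 |
|---|---|---|---|---|
| 2 | 8 | 33.7% | 25.0% | 15.8% |
| 3 | 11 | 43.1% | 30.6% | 18.0% |
| 4 | 14 | 51.2% | 34.8% | 19.8% |
| 5 | 17 | 58.2% | 38.7% | 21.1% |

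**Step 4: fewer samples.** If only the first sample were tested, m = 2 + k. Under independence this gives 1 − 0.95⁴ = 18.5% for k = 2 and 1 − 0.95⁷ = 30.2% for k = 5.

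**Step 5: power after adjustment.** With one biomarker test and Holm over three co-primaries, the first step is 0.05/3 = 0.0167. At 66 and 132 with δ = 0.5, noncentral-t power is 0.879 one-sided (from 0.952) and 0.816 two-sided (from 0.910). These are minimum values for the biomarker, because Holm relaxes the threshold once another co-primary has been rejected.

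**The case against.** **The success rule is assumed.** Section 2.8 gives a significance level and does not say that one significant result is enough. The Abstract words its expectation jointly: more RDS, more surfactant use and altered biomarkers. If all three objectives had to succeed, the error rate would not inflate across them and power would fall instead. This stands as a condition on the figures. It does not settle the matter, because the protocol states neither rule, and an all-must-succeed rule would still leave open which biomarker and time point must succeed.

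**The test count is an upper bound.** Section 2.5 makes the 48–72 h sample depend on stability and clinical indication, and day 7 is optional. That stands, and Step 4 shows the effect.

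**The list may already be fixed.** The Discussion says the ELISA kits were technically validated in advance, and the ethics committee may hold a fuller protocol. A reader might infer that the markers will be picked after the data are seen. The documents do not support that; they show only that no public record would allow a check.

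**This is an observational cohort.** Strict family-wise control is less settled here than in a confirmatory trial, and the authors foresee later multicentre validation. That bears on how strict the control should be. It does not excuse the lack of a declared lead comparison in a study that calls its biomarker objective co-primary and powers for it.

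**Conclusion.** The concern holds. The plan applies 0.05 to an open-ended primary family with no lead biomarker, lead time point, success rule or adjustment, so its family-wise error rate is uncontrolled and cannot be determined from the documents. If any one significant test counts, the rate is about 14% for three independent tests. For 2 to 5 assumed biomarkers at three time points it is about 34–58% under independence, 25–39% at correlation 0.5 and 16–21% at correlation 0.8.

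A reader might go further and infer that a positive primary result is likely to arise by chance. That is not shown. The rate passes 50% only from 14 tests, meaning at least four biomarkers at all three times with near-independent results. The number of biomarkers is not given, and correlation is to be expected.

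**What to change.** Before any participant sample is assayed, including for the preliminary analysis at 60 participants:

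1. Deposit the full biomarker list and time points in a time-stamped embargoed registration, or sealed with the ethics committee. Novelty stays protected.
2. In section 2.8, name one biomarker at the first (24 h) sample as the biomarker co-primary.
3. State the success rule. If any one co-primary suffices, test that biomarker, RDS and surfactant use with Holm at overall 0.05. If all must succeed, say so; each can then stay at 0.05.
4. Report other biomarkers and time points as secondary, with false-discovery-rate control.
5. State the sidedness, and restate power at the first Holm step of 0.0167.

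The cost is a paragraph in section 2.8, one filing and some power: 0.879 one-sided or 0.816 two-sided instead of the stated 0.952. The loss for RDS and surfactant use cannot be given, because the protocol reports no power for them. A larger sample is not required. If the sponsor wished to keep 0.95 one-sided power at the first Holm step, it would take 87 + 174 = 261 neonates instead of 198.

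### A normality test selects the biomarker comparison, and effect measures are named only for the normal branch

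*Protocol article*

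**What the plan says.** Section 2.8 (Statistical analysis) compares each biomarker between groups at each time point. It uses Student's t-test for normal data and the Mann-Whitney U "test when normality is not assumed". Normality is checked by Shapiro-Wilk. The effect measures follow the same split: "For normally distributed biomarker data, standardized mean differences between groups will be reported as Cohen's d and Glass's delta". No effect measure, interval or transformation is named for the other branch.

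For longitudinal trends the section plans repeated-measures ANOVA or linear mixed-effects models, chosen according to distribution and completeness, with the Friedman test as an option for non-parametric repeated data. Gestational age enters as a covariate in those models judged relevant.

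Section 2.3 (Sample size calculation) sizes the study on a biomarker difference of Cohen's d = 0.5 and calls the biomarkers co-primary. It says that "the higher power threshold of 0.95 was chosen to ensure adequate sensitivity for detecting clinically meaningful biomarker differences", and concludes: "This configuration provides robust power to detect moderate effect sizes over 0.5 with high reliability".

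**The concern.** The co-primary biomarker question is how far cholestasis exposure shifts lung-injury markers. The natural answer is an estimate with an interval, set against the 0.5 SD for which the study was sized. The text provides for such an estimate in one branch only, and a significance test decides which branch a marker enters.

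That test depends on sample size. With the same underlying skew, a large sample tends to fail it and a small one tends to pass. The number of samples falls with age by design: the 48–72 h sample needs clinical stability and an indication, and the day 7 sample comes only from longer stays (section 2.5). The Discussion also plans a preliminary biomarker analysis once 60 participants are enrolled. A marker could therefore change its test and summary between ages, or between the preliminary and final analyses, with no change in its biology.

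A marker that leaves the normal branch may lose more than Cohen's d. Mann-Whitney takes no covariate, so the gestational-age adjustment is lost in that comparison. Friedman tests change over time within neonates, so it cannot supply the group contrast.

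**Working it through.** **1. The plan's own figure.** Inputs from section 2.3: one-sided t-test, d = 0.5, α = 0.05, target power 0.95, 66 exposed and 132 unexposed.

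- Noncentrality = d / √(1/n₁ + 1/n₂) = 0.5 / √(1/66 + 1/132) = 3.317, with 196 degrees of freedom.
- One-sided power from the noncentral t = 0.9516. The article states 0.952, so the figure is reproduced.
- 65 v 130 gives 0.9490, so 66 v 132 is the smallest exact 2:1 design reaching 0.95.
- The two-sided test at the same sizes has power 0.910. This is the reference for the two-sided simulations in step 4.

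**2. Which branch a skewed marker enters.** The documents give no biomarker distribution and no number of day 7 samples. Assumptions: log-normal concentrations, log-SD 0.3 or 0.5 (coefficient of variation √(exp(σ²) − 1) = 31% or 53%), Shapiro-Wilk at 0.05, and 15 exposed v 30 unexposed at day 7. Simulated share of samples rejected as non-normal:

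| log-SD | n = 132 | n = 66 | n = 30 | n = 15 |
|---|---|---|---|---|
| 0.3 | 96% | 69% | 37% | 19% |
| 0.5 | 100% | 98% | 72% | 39% |

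If both groups must pass for the t-test and Cohen's d, the pass rates multiply. At log-SD 0.3:

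- 66 v 132: (1 − 0.69) × (1 − 0.96) = 0.31 × 0.04 ≈ 0.012. Direct simulation gives 1 to 2%.
- 15 v 30: (1 − 0.19) × (1 − 0.37) = 0.81 × 0.63 ≈ 0.51. Direct simulation gives 51%.

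At log-SD 0.5 direct simulation gives about 0% and 17 to 18%.

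**3. If the data are truly normal.** At 66 v 132 at least one group is still rejected in about 10% of trials, as expected from two tests at 5% (1 − 0.95² = 0.0975). So even a normal marker can lose its named effect measure by chance.

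**4. Power.** With a shift of 0.5 SD on the log scale and 66 v 132, two-sided at 0.05, the two-stage rule has power 0.89 to 0.90 and a Welch test on logs 0.90 to 0.91. In one-sided testing Mann-Whitney keeps about 94 to 95%. The gate costs almost no power at full size.

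**5. What could be set against d = 0.5 in the other branch.** Under a normal shift on the raw or log scale:

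- P(exposed > unexposed) = Φ(0.5/√2) = 0.638.
- Rank-biserial correlation = 2 × 0.638 − 1 = 0.276.
- At 66 v 132 the standard error of that probability is about 0.043, so the approximate 95% interval is 0.638 ± 1.96 × 0.043 = 0.554 to 0.722.
- On the log scale, 0.5 SD is a geometric mean ratio of exp(0.5 × 0.3) = 1.16 at log-SD 0.3 and exp(0.5 × 0.5) = 1.28 at log-SD 0.5. The ratio alone therefore does not show whether 0.5 SD was reached; the log-scale standardized difference must accompany it.

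**The case against.** A reader might infer that non-normal markers will be reported by p-value alone, or that they cannot be set against 0.5 SD. The article says neither. It is a condensed text, and a fuller protocol or analysis plan may name a rank-based estimate. Step 5 also shows that such an estimate can be compared with d = 0.5. Both stronger readings rest on silence and should not be asserted.

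Nor is it right that no adjusted estimate is planned at all. Section 2.8 plans mixed models and a gestational-age covariate, and the Discussion says that models incorporate gestational age, sex and perinatal infection. A mixed model can give group differences with intervals. This answers part of the concern, but not all of it: those models are described for longitudinal trends, their choice also depends on the data distribution, and no reported measure is fixed for them.

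The size of the problem rests on assumptions. Section 2.6 withholds the identity of the markers, so their skewness is unknown, and the 15 v 30 at day 7 is illustrative. At log-SD 0.5 the t-test branch is reached at that size in only about 17 to 18% of trials, so the switch between ages is less marked for a more skewed marker. Finally, a log transformation of every marker is one sound remedy among several.

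What stands is what the article itself fixes: the normality test as selector, and effect measures tied to its result.

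**Conclusion.** The point holds as a weakness in estimation and consistency. Section 2.8 makes a sample-size-dependent test the selector for a co-primary comparison, and it names between-group effect measures for one branch only. The Mann-Whitney branch has no named estimate or interval and no route to the planned covariate, and the Friedman option does not address the group contrast.

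If markers are log-normal with log-SD between 0.3 and 0.5, nearly every marker at 66 v 132 falls into the branch without a named effect measure. At an assumed 15 v 30 it falls there in about half of trials (log-SD 0.3) to just over four fifths (log-SD 0.5). If the markers are close to normal, the effect is confined to roughly one comparison in ten at full size. The stated sample size is reproduced and is not in question, and power is essentially unchanged. This is a cheap improvement, not a flaw that threatens the study.

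**What to change.** Drop Shapiro-Wilk as the selector. Fix in advance one primary between-group estimate with a 95% confidence interval for every biomarker at every time point.

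- **Preferred:** a linear (mixed) model on the log scale with gestational age as covariate. Report the geometric mean ratio together with the log-scale standardized difference, so that the result can be read against 0.5. Keep Mann-Whitney as a sensitivity analysis.
- **Minimum:** keep the present tests, but report a Hodges-Lehmann shift or a rank-biserial correlation with its interval for every marker, whatever the normality result.

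The cost is a few sentences in section 2.8 and a little more analysis work. The sample size of 198, the blood sampling and the assays do not change. One drawback is that a log scale may suit some markers less well; if so, name the alternative scale for that marker beforehand. The wording is best settled before the preliminary biomarker analysis planned at 60 participants.
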